### Statistical analyses

Data will be recorded in the digital study database and will be analyzed by a researcher blinded to the study groups the patients entered into.

Variations in case mix between centers can influence the interpretation of outcome data. Therefore, for each of the data sets collected, differences in outcome variable between the services will be tested using multiple MANCOVA’s, entering various indicators of case mix as co-variates (i.e. age, gender, ISS, number of complications, etc).

Insole pressures will be presented as mean ± SD. Statistical analysis of pressures involves repeated-measures two way ANCOVA using time as the within-group factor and treatment protocol as the between-group factor. Post-hoc group comparison at the different time points is only performed when the overall repeated-measures tests are statistically significant. A Bonferroni approach will be used to avoid spurious false positive findings. All scores will be tested for normality using the Shapiro-Wilk test. Multilevel factor analysis will be performed to determine independent factors related to the primary outcome parameter functional outcome.

Statistical analysis will be performed using the Statistical Package for Social Sciences (SPSS, IBM), version 23. Level of significance will be set at alpha< 0.05.

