### Hypothesis

#### Hypothesis 1

The permissive weight bearing protocol will lead to 1A: a better outcome at activity level (as measured with the Lower Extremity Functional Scale (LEFS)), 1B: a better early recovery at function level (as measured with the Brunnstrom Fugl-Meyer (BFM) test), 1C: a better participation (as measured with the SF-36) and 1D: a better quality of life (as measured with the EQ-5D-5L) in the first 6 months post-surgery, as compared to patients who are treated according to current standard guidelines. It is expected that in the long-term (i.e. 1 year) functional outcome will be similar between the treatment groups and will therefore not be the primary focus of this study [3]. We have chosen for the three scales mentioned above to cover the major outcome levels in the ICF model [17].

#### Hypothesis 2

The permissive weight bearing protocol for trauma patients with fractures of the lower extremities is more cost-effective compared to the non-weight bearing protocol and current guidelines.

#### Hypothesis 3

The rate of complications (e.g. failure of osteosynthesis, secondary displacement of fracture parts, non-union, infections) is equal or lower in patients who are treated according to the permissive weight bearing protocol compared to patients treated according to standard current guidelines.

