### Demographic and medical variables

The following variables will be recorded:GenderAgeDate and time of traumaType of fractureInjury severity score (ISS)Type of operationLength of stay in hospitalComplications before rehabilitationWeight bearing policyTime between accident and weight bearingDate of 100% weight bearing (insoles)Complications during rehabilitation.

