### Secondary outcome measures

Function (Brunnstorm Fugl-Meyer)Participation (SF-36)Improvement in quality of life (EQ-5D-5L)Reduction in health and society costs (RUM)Total complication rate

Outcome variables gauging functional outcome:Score on Brunnstrom Fugl-Meyer [21] at 0, 2, 6, 12 and 26 weeks post-surgeryScore on SF-36 [22] at 0, 2, 6, 12 and 26 weeks post-surgeryScore on EQ-5D-5L [23] at 0, 2, 6, 12 and 26 weeks post-surgery

Outcome variables gauging complication rate:Failure of the osteosynthesis, defined as loosening or breakage of implantsMigration of fracture parts, defined as > 3 mm articular step-off and/or varus/valgus malalignment > 5 degreesInfection, defined as (but not limited to) purulent wound drainage, inflammation, erythema, fever, increased white blood cell (WBC) count, increased C-reactive protein (CRP) and/or increased erythrocyte sedimentation rate (ESR), necessitating admission for intravenous antimicrobial treatment and/or revision surgeryNon-union, defined as no radiographic union achieved after 6 months or no progress in healing

Outcome variables gauging compliance [5, 6, 24–26]:Self-reported adherence to the fracture-related weight bearing protocol, will be recorded in medical records by physical therapists.Peak load (% body weight) and step duration (in seconds) as measured by the Sensistep [27] insole pressure measurement system. The Sensistep will be used by the patient only during daytime. The measurements with the Sensistep will continue until the patient has shown 100% weight bearing. The time for the latter to occur, may differ between patients.

Brunnstrom Fugl-Meyer: This is a test that evaluates the degree of synergy formation. The test consists of 55 test items that can be scored on an ordinal 3 - point scale (0–2 points). The total test consists of an examination of the upper extremity, an examination of the lower extremity and an examination of the balance. For our study we will only use the examination of the lower extremity. The maximum total score concerning the lower extremities is 34 points [21].

SF-36: This is a multi-purpose, short-form health survey with 36 questions. It yields an 8-scale profile of functional health and well-being scores, as well as psychometrics-based physical and mental health summary measures, and a preference-based health utility index. The higher the score the better the participation [22].

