EuroQol: Both generic quality of life, as well as utilities, will be derived by means of the EQ-5D, which both will be administered to the patients. The EQ-5D is chosen because it is a widely used quality of life instrument (nationally and internationally) and it is recommended by the Dutch guidelines [28]. The EQ-5D contains 5 dimensions of health-related quality of life, namely mobility, self-care, daily activities, pain/discomfort and depression/anxiety. Each dimension can be rated at five levels ranging from ‘no problems’ to ‘major problems’.

Resource Use Measurement (RUM): for this study we will develop a RUM instrument especially designed for this group, based on existing questionnaires, which will measure all relevant costs aspects [29]. A resource use measure counts the frequency of defined health system resources; such as allowable charges, paid amounts, or standardized prices. Current approaches for measuring resource use range from broadly focused measures, such as per capita measures, which address total healthcare spending per person, to those with a more narrow focus, such as measures dealing with healthcare spending for an individual procedure.

Complication score:

Measurements will be taken at 6, 12, and 26 weeks post-surgery.

During scheduled visits to the physician, signs of osteosynthesis failure / infection / non-union / delayed union will be recorded in the study database.

Radiographic evaluation by a radiologist blinded for treatment allocation will be done at the same time intervals as the scheduled visits to the physician. Radiographs will be scored for signs of osteosynthesis failure / infection / non-union and migration of fracture parts, and results will be recorded in the study database.

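### The case-mix covariates include the number of complications, not limited to events before rehabilitation, although complications are also an outcome that the aftercare may change

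*Protocol article*

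**What the plan says.** The Statistical analyses section gives the reason for adjustment: "Variations in case mix between centers can influence the interpretation of outcome data". It then states the scope: "for each of the data sets collected, differences in outcome variable between the services will be tested using multiple MANCOVA’s". The covariates follow: "entering various indicators of case mix as co-variates (i.e. age, gender, ISS, number of complications, etc". Nothing limits the complication count to a period, and no outcome is exempted.

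Elsewhere the protocol treats complications as a result of care:

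- Secondary outcome measures lists "Total complication rate", made up of implant failure, displacement, infection and non-union.
- Hypothesis 3 states that the rate "is equal or lower in patients who are treated according to the permissive weight bearing protocol".
- The complication score has its own schedule: "Measurements will be taken at 6, 12, and 26 weeks post-surgery".
- Demographic and medical variables records complications arising before rehabilitation and, as a separate item, "Complications during rehabilitation". The analysis section does not say which of the two is meant.

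**The concern.** Age, gender and ISS are settled before aftercare begins. A complication count that includes events during rehabilitation is not. It may be changed by the weight-bearing protocol and may itself lower LEFS, so it can lie on the path from treatment to the primary outcome. Conditioning on it moves the estimate from the total effect of the protocol towards the part that does not act through complications. If complications and LEFS also share an unmeasured cause, such as severity of the local injury, conditioning on complications can create a further association between protocol and LEFS.

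More is at stake here than in a randomised trial. Hospitals, not patients, determine the treatment group (two intervention and four control hospitals), so the covariates carry much of the protection against confounding. The distortion can also run in the unsafe direction: if permissive weight bearing raised the complication rate, adjustment would hide the resulting loss of function.

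**Working it through.** **Timing.** LEFS is taken at weeks 0, 2, 6, 12 and 26, and complications are scored at weeks 6, 12 and 26. Non-union is defined partly by absence of union after 6 months, so a full count may be settled only around the last LEFS visit. For LEFS at weeks 2, 6 and 12, such a count could include events later than the outcome being adjusted.

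**The plan's own figure.** The protocol gives no figure for the adjusted analysis. Its planning difference follows from Sample size calculation: control mean 65, improvement 10%, so 0.10 × 65 = 6.5 LEFS points.

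**Inputs for the size.**

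- Complication rates (Background): 10% in the retrospective series under permissive weight bearing; a literature average of 10–20%, with a maximum of 37%.
- LEFS loss per complication: not in the documents. Assumed to be 5, 10 or 15 points.

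**Formula.** In a linear model with no common cause of complications and LEFS,

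total effect = direct effect + (loss per complication) × (control rate − permissive rate).

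Adjusting for complications returns the direct effect, so the amount removed is the last term.

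| Control vs permissive rate | Loss 5 | Loss 10 | Loss 15 |
|---|---|---|---|
| 10% vs 10% | 0 | 0 | 0 |
| 15% vs 10% | 0.05 × 5 = 0.25 | 0.50 | 0.75 |
| 20% vs 10% | 0.10 × 5 = 0.50 | 1.00 | 1.50 |

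With the total effect set at 6.5, the last row leaves adjusted estimates of 6.0, 5.5 and 5.0. The amounts removed are 0.5/6.5 = 8% to 1.5/6.5 = 23% of the planned difference.

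**Simulation check** (1,000,000 patients per scenario). At 20% vs 10% the bias was −0.50, −1.01 and −1.48, in line with the formula. Adding an assumed unmeasured common cause (standard normal, 5 LEFS points per SD, probit coefficient 0.5 on complications) made it −0.91, −1.42 and −1.92, about 0.4 points more. At equal rates it stayed within 0.02 of zero with or without the common cause.

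**Opposite direction.** With the rates reversed (10% control, 20% permissive), the formula changes sign: adjustment would raise the estimate by 0.5 to 1.5 points and mask harm.

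The 37% figure is a literature maximum and is not used to size the problem.

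**Complication outcome.** If the outcome is the complication count and the covariate is the same count, the covariate explains the outcome completely and no treatment comparison is left to estimate.

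**The case against.** The best defence is that the text calls these variables case-mix indicators and places the complication count beside three pre-treatment characteristics. Since complications before rehabilitation are recorded separately, the authors may have meant only those. That reading is possible, so the wording is ambiguous and does not prove a post-treatment adjustment. It still does not meet the point. An unqualified count naturally covers both recorded items, and while the open ending of the list can add covariates, it cannot remove or narrow one that is named.

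It is also fair to say that nobody would sensibly adjust an outcome for itself. That part is best seen as loose drafting that needs an explicit exception.

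Two stronger readings are tempting and do not stand:

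- *That fracture type and week-0 LEFS are left out of the adjustment.* The list is open-ended, both variables are collected, and a full analysis plan, not shown here, may name them. They are unnamed, not excluded.
- *That the adjusted effect is biased.* Hypothesis 3 allows equal complication rates, and the permissive figure of 10% lies at the lower end of the literature average, so no difference is within the protocol's own range. The distortion is then about zero.

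**Conclusion.** The point holds as a fault of wording with real consequences if followed. A named covariate, applied to every outcome and not limited to events before rehabilitation, overlaps a secondary outcome that the protocol itself links to treatment. The adjusted LEFS comparison may therefore be distorted.

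The size cannot be fixed from the documents. It is about 0 at equal rates. At 20% vs 10% it is roughly 0.5 to 1.5 of 6.5 points, on the assumption of 5 to 15 LEFS points lost per complication, a linear model and no common cause. An assumed common cause takes it to about 0.9 to 1.9. When permissive weight bearing has fewer complications, these scenarios move the estimate towards no effect.

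That fracture type and week-0 LEFS are not named is a secondary matter of clarity, not an established omission.

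**What to change.** In Statistical analyses:

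1. Replace the number of complications by complications before rehabilitation, or delete it.
2. State that no covariate arising after the start of aftercare enters the outcome models.
3. State that the complication outcome is not adjusted for complications.

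This takes two or three sentences and no new data, because the earlier complications are already a separate item. Replacing one count by another uses no extra degrees of freedom.

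As a low-cost addition, name fracture type among the covariates, and week-0 LEFS if it is taken before weight-bearing aftercare begins. The timing must be stated, because Data collection places week 0 as early as possible after injury while the outcome schedule counts from surgery.

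Fracture type should be grouped coarsely. Three groups would cost 2 degrees of freedom and week-0 LEFS 1, so 3 in all. A full set would be heavy for the 102 evaluable patients planned: six fracture locations (5), AO type (2), type of operation (at least 1), and age, gender, ISS, earlier complications and week-0 LEFS (5) come to at least 13.

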### Sample size calculation

To date, no exact data on differences in functional outcome (LEFS) between the two different aftercare treatments for patients with fractures of the lower extremities are available. In two studies, the LEFS is expected to be 65 points (SD 10) in the non-weight bearing group [18, 19]. In this study we consider an increase in LEFS of 10% or more in the permissive weight bearing treatment group. In order to detect a difference between two independent means (two groups), assuming that an equal number of patients in both groups will be included, with an alpha of 5% and beta of 20% (power 80%), the sample size should be at least 51 for both groups, thus leading to a total number of 102. Anticipating a 20% drop out and 10% more patients to obtain equal groups, a total of 134 patients have to be recruited.

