### Primary outcome measures

ADL with Lower extremity functional scale (LEFS).

Outcome variables gauging functional outcome:

Score on LEFS [20] at 0, 2, 6, 12 and 26 weeks post-surgery.

LEFS: This is a questionnaire containing 20 questions about a person’s ability to perform everyday tasks. The LEFS can be used by clinicians as a measure of patients’ initial function, ongoing progress and outcome, as well as to set functional goals. The LEFS can be used to evaluate the functional impairment of a patient with a disorder of one or both lower extremities. It can be used to monitor the patient over time and to evaluate the effectiveness of an intervention. The questionnaire’s rating scale consists of 80 points. The lower the score the greater the disability [20].

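### Multilevel factor analysis is the wrong method for finding which factors are independently associated with LEFS; the sentence should name a regression model

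*Protocol article*

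**What the plan says.** The Statistical analyses section of the protocol article names three kinds of analysis.

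- Multiple MANCOVAs test differences in outcome between the services, "entering various indicators of case mix as co-variates (i.e. age, gender, ISS, number of complications, etc").
- For the insole data, "Statistical analysis of pressures involves repeated-measures two way ANCOVA", with time and treatment protocol as factors.
- For functional outcome there is one further sentence: "Multilevel factor analysis will be performed to determine independent factors related to the primary outcome parameter functional outcome".

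The section on primary outcome measures makes the LEFS the measure of functional outcome, scored "at 0, 2, 6, 12 and 26 weeks post-surgery". The article does not say which variables would enter the factor analysis, whether LEFS would be one of them, what the levels are, or whether any later step would relate the resulting factors to LEFS.

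**The concern.** The sentence joins an aim to a method that does not serve it. The aim is to learn which patient, injury or treatment characteristics go with a better or worse LEFS once the others are taken into account. That is a regression question. Factor analysis asks a different one: how many latent dimensions account for the correlations among a set of measured variables. The word factor means a predictor in the aim and a latent variable in the method, which is probably how the mismatch arose.

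An analyst who follows the sentence literally obtains loadings that do not answer the question. An analyst who sees the mismatch has to choose another model, possibly with the data in hand. That freedom matters in a non-randomised study whose own plan expects case mix to differ between centers.

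**Working it through.** The plan attaches no figure to this analysis, so there is none to reproduce. The sample size calculation serves a comparison of two means and plays no part here. The check sets the stated aim against what the named method produces.

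**1. What the aim needs.** For patient i at visit t, with candidate factors x₁ to xₚ:

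LEFSᵢₜ = β₀ + β₁x₁ᵢ + … + βₚxₚᵢ + uᵢ + eᵢₜ

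The answer is the set of β's with their intervals, each adjusted for the other factors. The patient term uᵢ is needed because LEFS is measured at five visits.

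**2. What the named method gives.** A factor model for a vector z of variables is z = μ + Λη + ε, so that Cov(z) = ΛΦΛ′ + Ψ. The multilevel version splits the covariance into a within part and a between part and gives each this structure. The output is loadings, factor covariances and residual variances. All variables stand on the same side of the equation. None is the outcome, and no parameter is the effect of one variable on LEFS with the others held fixed.

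**3. The two ways LEFS could be handled.** The text does not say which applies.

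- *LEFS left out of z.* The loadings depend on the covariates alone and cannot reflect LEFS. A small single-level simulation (n = 102, four covariates) illustrates this. The loadings were 0.86, 0.66, 0.57 and 0.53, whether LEFS depended on the first covariate or on none. A regression with LEFS as dependent variable separated the two cases: the first covariate's coefficient was 7.03 (p < 0.001) in one and −0.75 (p = 0.67) in the other. The equal loadings follow by construction, so this is illustration and not proof.
- *LEFS included in z.* With one factor of variance 1, the model implies Cov(LEFS, xⱼ) = λ_LEFS × λⱼ. That does express an association, but a symmetric one through the shared dimension, not an adjusted coefficient. Coefficients could be derived afterwards from the fitted covariance matrix, or factor scores could be entered in a regression. Neither step is stated.

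**4. Whether another analysis covers the aim.**

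| Analysis in the section | Stated use | Stated for determinants of LEFS? |
|---|---|---|
| MANCOVAs | Differences in outcome between services, adjusted for case mix | No; covariate coefficients would be a by-product |
| Repeated-measures two-way ANCOVA | Insole pressures | No |
| Multilevel factor analysis | Factors associated with functional outcome | Yes, but the method does not fit |

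**5. What depends on it.** The primary research question in the Background compares the two protocols on functional outcome. The secondary questions concern costs and complications. All three hypotheses are contrasts between the two protocols. None asks which factors determine LEFS, so the affected analysis is ancillary.

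**The case against.** The strongest reply is that this is a slip in naming. The sentence itself supplies an outcome and speaks of factors associated with it, so a sensible analyst would read it as a multilevel regression. The model form may also be set out in a full protocol or analysis plan that is not shown. The first part is probably right about intent, but it remains an inference. The second part excuses missing detail, whereas here the article names a specific method and the name is wrong.

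The reply does succeed in limiting the point. A reader might infer several stronger conclusions that the article does not support:

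- *That the main comparison of protocols is undermined, or that a research question goes unanswered.* The case-mix-adjusted MANCOVAs appear to cover the group comparison, and no research question or hypothesis asks for determinants.
- *That the method fails because it would have only six level-2 units.* This assumes that hospital is the second level. The levels are not defined. With visits nested in patients, level 2 would be the patients, between 102 and 134 by the sample size section.
- *That the method yields no association with LEFS at all.* If LEFS is among the analysed variables, its loading carries some association, though not an adjusted one.
- *That this error leaves the plan without a hospital-adjusted LEFS effect.* Clustering by hospital is a separate question. By the Population section, two hospitals supply the permissive group and four others the control group, so hospital and protocol are tied together by design. Correcting the term would not untie them.

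**Conclusion.** The point holds as a wrongly named method. The Statistical analyses section assigns factor analysis to a question that needs a model with LEFS as dependent variable, and no other analysis is stated for that question. As written, this one ancillary analysis cannot deliver its aim. The main group comparison is not directly affected, on the reading that it falls under the MANCOVAs; the article's reference to services leaves that reading likely but not certain.

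The size is a matter of kind and not of degree: no sample size, power or error rate changes. The conclusion rests on the ordinary meaning of factor analysis and on the absence of any stated second step that would bring LEFS in as an outcome. That a multilevel regression was meant is probable but unconfirmed.

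**What to change.** Replace the sentence with one that names a multilevel (mixed-effects) linear regression:

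- LEFS is the dependent variable, with repeated visits nested within patients.
- Treatment protocol and pre-treatment factors are entered together. Age, gender, ISS, fracture type and type of operation are already on the list of recorded variables.
- Coefficients are reported with 95% confidence intervals.
- The levels are stated explicitly.

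If a hospital level is added, say that there are six hospitals and that protocol is fully nested in hospital (two permissive, four control). The hospital variance will then be imprecise, and the protocol coefficient needs small-sample caution. Remaining details, such as how visit week enters the model, can be left to the analysis plan.

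The cost is a sentence or two of text. No new data, visits or patients are needed. The change should be made before the data are analysed, so that the choice of model is not made with results in view.
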